**BARRETOS-SP**

**2020**

**SUMMARY**

**Introduction:**Cancer is an extremely aggressive disease, and anxiety and depression are consequences that some patients may develop, from the time of diagnosis, continuing throughout the course of treatment. One of the measures to control cancer is surgery to remove the tumor. The surgical procedure is often a difficult experience for patients and their families, and patients in the preoperative period are often encountered with psychological symptoms of anxiety and depression. Studies show that patients welcomed by family members in the preoperative period significantly reduce the symptoms of anxiety, fear and panic compared to those who were only accompanied by health professionals. **Goals:**To analyze the emotional repercussion of patients diagnosed with cancer classified as ECOG PS 0 and 1 according to the type of transport to the operating room. **Methodology:**Randomized clinical trial, with prospective collection, which will take place at the Barretos Cancer Hospital. For the sample calculation,considering a α error of 0.05 and a power of 1 – β of 0.80, a sample size of 176 patients was reached, with 88 patients allocated to the stretcher group, and 88 patients allocated to the ambulation group.**Expected results:**It is expected to find some emotional change in the degree of anxiety and satisfaction of patients according to the modification of their type of transport to the operating room, and it is possible to modify the hospital routine related to the way these patients are conducted.

**Keywords:**Anxiety, depression, operating room, ambulation, preoperative.

**1. INTRODUCTION**

As described by the World Health Organization (WHO), it is indisputable that cancer is a public health problem, especially among developing countries, where it is expected that in the coming decades the impact of cancer on the population will correspond to 80% of the more than 20 million new cases estimated for 2025 ([1](#_ENREF_1)).

Cancer is an extremely aggressive disease, and the science of the disease has a great impact on the patient's life, and can cause physical and emotional changes. Anxiety and depression are consequences that some patients can develop, from the time of diagnosis, continuing throughout the course of treatment ([2](#_ENREF_2), [3](#_ENREF_3)).

There are several types of cancer treatment, including surgery, chemotherapy, radiotherapy, hormone therapy, immunotherapy and rehabilitation. And some types of treatments bring numerous side effects related to the fact that they do not exclusively reach cancer cells, among them the following stand out: nausea, vomiting, alopecia and burns that weaken the patient and shake his emotional state, which corroborates the hopelessness and suffering of the patient diagnosed with cancer ([4](#_ENREF_4)).

One of the measures to control cancer is surgery to remove the tumor, however, although this is often possible, some surgical practices can have serious physical consequences, such as surgical procedures with mutilation, and the fear of surgical intervention in some cancer patients is so great that pathological anxiety or distorted thoughts result in refusal of treatment in more than 5% of cases ([5](#_ENREF_5), [6](#_ENREF_6)).

Patients in the preoperative period are often found with psychological symptoms of anxiety and depression, and the ideal would be that there are no concerns other than those caused by the disease itself. However, anticipation of pain, separation from family, loss of independence, fear of disability, in addition to fear of the procedure itself and death, end up being factors that frequently trigger these symptoms during this period ([7](#_ENREF_7)).

In a previous study, it was observed that preoperative anxiety was present in about 80% of adult patients who were waiting for some type of surgery. In view of this, anxiety deserves due attention from the health team, as it can influence the patient's response to treatment and cause negative effects on their postoperative recovery. In addition, anxiety causes physiological changes, such as tachycardia and arterial hypertension, with a consequent increase in oxygen consumption and worsening of the evolution of the disease ([8](#_ENREF_8)).

The surgical procedure is often a difficult experience for patients and their respective families, and requires a series of affective mobilizations to deal with the anxiety and stress of the situation. Any surgical act is considered a critical situation capable of arousing individual behaviors, influenced by multiple physical and emotional factors ([9](#_ENREF_9)).

One of the strategies used to reduce anxiety and depression levels during the preoperative period is to provide information about health conditions, procedures performed and the participation of the family member at this time ([9](#_ENREF_9)).

Studies show that patients welcomed by family members in the preoperative period significantly reduce the symptoms of anxiety, fear and panic compared to those who were only accompanied by health professionals. The presence of the family member mainly reduces the feeling of anxiety in the preoperative period, characterized as a feeling of fear and apprehension of the unknown, contrary to what happens when there is a single presence of the nursing professional, increasing the anxiety rates in relation to patients who were not accompanied by their family members. Thus, it is possible to see the essential relationship between the presence of family members and the reduction of anxiety in such a critical period, which is the preoperative period ([8](#_ENREF_8)).

Another important point is that in the literature it is very common to find articles that define the importance of intra-hospital transport for diagnostic or therapeutic purposes of critical patients, including those who have some type of cancer being treated in the Intensive Care Unit (ICU). The transfer of these patients depends directly on the planning and organized action of the multidisciplinary team, as well as the choice of indispensable equipment, which is necessary because critically ill patients are more susceptible to physiological changes, which can cause complications along the way. However, little has been studied about transportation to the operating room when the patient is in a non-critical state ([8](#_ENREF_8), [10](#_ENREF_10), [11](#_ENREF_11)).

Kojima e*t al.* ([12](#_ENREF_12)) conducted a study between October of 1998 and September of 2000 with patients aged 15 to 80 years who were to undergo some type of surgery, but the study did not specify the previous diseases or the reason for the surgery, giving due importance only to the way of transportation to the operating room: one through the use of a stretcher and the other through ambulation, also analyzing the patients' degree of awareness of the medications used, reaching the following result: patients who walk feel calmer in the preoperative period. The use of stretchers makes them more anxious, distressed and even inferior when talking to other people since they remain lying down and draw more attention wherever they go. All of this reflects the stress caused by this type of transport, and it is understood that ambulation reduces the level of anxiety caused by this type of transport. However, in this study, the diseases such as cancer, the degree of limitation of the patients, or the classification in the PS score of the patients submitted to the surgical procedure are not specified. Another important point is the wide spectrum of age range of the patients analyzed by the study, since it encompasses from adolescents to the elderly, generating many variables for a truthful analysis of the results.

1. **JUSTIFICATION**

Cancer patients present emotional changes from the moment of their diagnosis and throughout the treatment, for this reason, the study wants to observe if there is any change in the emotional responses, the degree of anxiety and the satisfaction of adult cancer patients classified as PS 0 and 1 according to the change in the type of transport to the operating room, replacing the use of stretchers (traditional model) with ambulation. In addition, there is a deficit of studies published in the literature on this topic, especially in cancer patients, and according to the final findings, it can change the daily practice in relation to the way these patients are taken to the operating room, reducing anxiety levels and thus resulting in a better recovery of the patient.

- 1. **Factor under Study**

Way of driving to the operating room (stretcher versus ambulation)

- 1. **Primary outcome**

Emotional impact according to the way they were driven to the operating room.

1. **OBJECTIVES**
   1. **Primary objective**

**3.1.1** Determine the anxiety levels of the patient diagnosed with cancer according to the type of transport to the operating room.**.**

**3.2 Secondary objectives**

**3.2.1** To analyze whether the type of transport of the patient classified as PS 0 and 1 has an influence on the degree of depression.

**3.2.2** To analyze whether the type of patient transport classified as PS 0 and 1 has an influence on the degree of patient satisfaction.

**3.2.3**Analyze the patient's anxiety according to the type of transport, according to gender.

**3.2.4** Analyze the patient's anxiety according to the type of transport, according to the socioeconomic level.

1. **METHODOLOGY**

**4.1 Design**

This is a randomized clinical trial, with prospective collection, to analyze the emotional repercussion of patients diagnosed with cancer classified as ECOG PS 0 and 1 according to the type of transport to the operating room.

**4.2 Sample**

To select these patients, we will use the fall risk assessment scale adopted in the hospital routine for patients over 60 years of age, together with the *Eastern Cooperative Oncology Group (ECOG PS)*scale (Table 1), with only patients being classified as no risk or with minimal risk,*,* according to the fall risk scale (Table 2), and patients with SP 0 and 1.

**Table 1 -ECOG Performance Status** (Grupo de Oncologia*Eastern Cooperative, [name].)*

| Degree | **ECOG PERFORMANCE STATUS** |
| --- | --- |
| 0 | Fully active, able to develop all your performance, without any restrictions. |
| 1 | Restrictions on strenuous activities, while maintaining normality in their daily practice. |
| 2 | He still retains his capacity for self-care, but he is unable to perform any work activity, and if he does, it is in less than 50% of waking hours. |
| 3 | Limited capacity for self-care; confined to a bed or chair for 50% of waking time. |
| 4 | Completely disabled, unable to exercise self-care, totally confined to a bed or chair. |
| 5 | Death |

**Table 2: -**SCALE FOR ASSESSING THE RISK OF FALLING (Adapted from Jonhs Hopkins 2007)

| Zero = No Risk 1-5 = Low Risk 6-13 = Moderate Risk > 13 = High Risk | |
| --- | --- |
| **Risk Factor** | **Punctuation** |
| 1. **Age**(select option 1) |  |
| •         60 – 69 years old | 1 |
| •         70 – 79 years old | 2 |
| •         Greater than or equal to 80 years old | 3 |
| 2. **Fall history** |  |
| •         Drop in the last 6 months before admission | 5 |
| 3. **Eliminations**(select option 1): |  |
| •         Incontinence | 2 |
| •         Urgency or change in frequency | 2 |
| •         Urgency/change in frequency and incontinence | 4 |
| 4. **Medications** |  |
| •         Use of 1 of the options | 3 |
| •         Use of 2 or more options | 5 |
| •         Underwent sedative procedures within the last 24 hours | 7 |
| 5. **Use of Equipment:**any equipment used by the patient, such as catheters, venipuncture, among others (select 1 option) |  |
| •         Presence of 1 device | 1 |
| •         Presence of 2 pieces of equipment | 2 |
| •         Presence of 3 or more devices | 3 |
| 6. **Mobility**(multiple selection allowed) |  |
| •         Needs assistance or supervision for movement, transfer or ambulation | 2 |
| •         Unstable gear | 2 |
| •         Visual and/or hearing impairment that affects movement | 2 |
| 7. **Cognitive**(multiple selection allowed): |  |
| •         Altered consciousness related to the environment | 1 |
| •         Impulsive | 2 |
| •         Lack of understanding of their physical and cognitive limitations | 4 |
| 8. **Special conditions:**According to the list: | No / Yes |

Health conditions and presence of chronic diseases – must be linked to item 8 of the scale:

Previous stroke, postural hypotension, dizziness, low body mass index, anemia, insomnia, incontinence or urinary urgency, arthritis, osteoporosis, metabolic alterations (e.g., hypoglycemia).

**Table 3 -**Medications related to the use of mean item 4.

| Atenolol | Dimenhydrinate | Regular Human Insulin | Nalbuphine | Sultamicilin |
| --- | --- | --- | --- | --- |
| Atracurium | Dipyridamole | NPH insulin | Naloxone | Succinylcholine |
| Atropine | Dipyrone | Potassium Iodide | Naproxen | Tracolimos |
| Methyl Blue | Dobutamine | Iodixanol (Visipaque Leaflet) | Neostigmine | Tacrolimus Topical |
| Benzydamine | Dopamine | Ioversol | Nifedipine | Theicoplanin |
| Betamethasone | Droperidol | Ipratropium | Nimesulide | Terbutaline |
| Bisacodyl | Epinephrine | Ipratropium + Fenoterol | Nitroglycerine | Thiabendazole |
| Bromopride | Ertapenem |  | Nitroprusside | Thiopental |
| Budesonide | Scopolamine | Dinitrate | Norfloxacin | Tramadol |
| Bupivacaine | Spironolactone | Itraconazole | Nortrititiline | Sodium Valproate |
| Captopril | Streptokinase | Ivermectin | Octreotide | Vancomycin |
| Carbamazepine | Ethylephrine | Lamivudine | Omeprazole | Warfarin |
| Carvedilol | Etomidate | Levofloxacin | Ondansetron | Vasopressin |
| Ceftriaxone | Phenazopyridine | Levomepromazine | Pancuronium | Verapamil |
| Ketamine | Phenytoin | Levothyroxine | Paracetamol | Voriconazole |
| Ketoprofen | Phenobarbital | Lindocaine | Paroxetine |  |
| Tromethamine ketorolac | Fenoterol | Lindocaine + Epinephrine | Pethidine |  |
| Cyclosporine | Fentalina | Lindocaine 25 mg/g + Prilocaine 25 mg/g 5g | Piperacillin |  |
| Cirpofloxacin | Phytomenadione (vitamin K) | Loperamide | Polymexin B |  |

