**4.4 Eligibility Criteria**

- Patients diagnosed cancer
- Age 18 years or older, up to 70 years old
- Both sexes
- Classified as PS score 0 or 1
- Patients who are rated Zero Risk or Low Risk by the falls risk assessment scale
- Indication for elective surgery

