**4.5 Non-eligibility criteria**

- Patients who, moments before surgery, present an adverse event that may jeopardize walking to the operating room.
- Patients who have a physical disability and need help to walk.
- Patients who have an indication for a bed in the Intensive Care Unit (ICU)
- Patients who have previously diagnosed psychiatric disorders (severe depression, anxiety disorder, panic, among others).
- ECOG patients > 1.
- Patients who do not have a companion on the day of surgery.
- Patients using anxiolytic and antidepressant medications.

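### The 0–5 fall-risk total can clear for walking a patient with unaided unstable gait, known postural hypotension or dizziness, or, in one narrow profile, a recent fall

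*Combined protocol and SAP*

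**What the plan says.** Table 2 in section 4.2 adds points over several items and bands the total as "Zero = No Risk 1-5 = Low Risk 6-13 = Moderate Risk". Section 4.4 admits "Patients who are rated Zero Risk or Low Risk by the falls risk assessment scale", that is, a total of 0 to 5. It also requires ECOG 0 or 1 and an age of 18 to 70.

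Three entries matter here:

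- Item 6 gives 2 points for "Unstable gear" (read here as a translation of unstable gait) and 2 for "Visual and/or hearing impairment that affects movement".
- Item 2 gives 5 points for "Drop in the last 6 months before admission".
- Item 8 is answered No or Yes, with no points printed. Its list begins "Previous stroke, postural hypotension, dizziness, low body mass index, anemia, insomnia", and the text says these conditions "must be linked to item 8 of the scale". It does not say what a Yes does to the total or to eligibility.

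Section 4.5 excludes patients with a physical disability who need help to walk, and "Patients who, moments before surgery, present an adverse event that may jeopardize walking to the operating room". Section 5.1 acknowledges a minimum risk of falls, relies on this scale to limit it, and provides the stretcher bearer and a family member as support on the way. Section 4.6 places the consent form after the transport and the questionnaires.

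**The concern.** Walking is the experimental intervention, and the fall-risk total is the main screen for who may be randomised to it. A low total means that few points have accumulated. It does not mean that no item bearing directly on walking is present. A patient who walks unsteadily, or who is known to become dizzy or hypotensive on standing, can sit inside the eligible range.

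The screen carries more weight than usual because consent follows the walk: the patient has no trial consent step beforehand at which to weigh the risk of falling. What is at stake is an avoidable fall in the walking arm. Eligibility is the same in both arms, so the comparison between them is not at issue.

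**Working it through.** **Inputs.** From Table 2: age under 60 = 0, 60–69 = 1, 70 = 2 (section 4.4 stops at 70); recent fall = 5; unstable gait = 2; sensory impairment affecting movement = 2; listed drugs none/one/two or more = 0/3/5; devices none/one/two/three or more = 0/1/2/3; item 8 = no printed points. The eligibility cut is a total of at most 5. Section 4.2 speaks of minimal risk where 4.4 says low risk; Table 2 has no minimal band, so the 4.4 wording is used. The item for needing assistance is set to 0, because 4.5 removes patients with a physical disability who need help to walk.

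**Formula.** Base total = age points + condition points. Spare points = 5 − base total. A patient stays eligible while the points from all other items do not exceed the spare points.

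| Condition | Base total: under 60 / 60–69 / 70 | Spare points |
| --- | --- | --- |
| Unstable gait | 2 / 3 / 4 | 3 / 2 / 1 |
| Unstable gait + sensory impairment | 4 / 5 / 6 | 1 / 0 / excluded |
| Postural hypotension or dizziness (item 8 Yes, no printed points) | 0 / 1 / 2 | 5 / 4 / 3 |
| Fall in last 6 months | 5 / 6 / 7 | 0 / excluded / excluded |
| Fall + gait + sensory impairment | 9 / 10 / 11 | excluded at every age |

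**What the spare points allow.**

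- *Unstable gait.* Under 60, one listed drug still passes (2 + 3 = 5). At 60–69 the same drug excludes (3 + 3 = 6), but two devices without a drug pass (3 + 2 = 5). At 70, one device passes (4 + 1 = 5).
- *Postural hypotension or dizziness.* Under 60, one drug plus two devices passes (0 + 3 + 2 = 5). At 60–69, one drug plus one device passes (1 + 3 + 1 = 5). At 70, one drug passes (2 + 3 = 5). Combined with unstable gait the totals are 2, 3 and 4, all eligible.
- *Recent fall.* Under 60 the total is exactly 5, so one device counted when the scale is scored excludes (5 + 1 = 6), as does one listed drug (5 + 3 = 8).

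**Check by enumeration.** Summing every combination of the scored items gives 3 × 2 × 3 × 4 × 4 × 2⁵ = 9,216 score profiles (age, fall, eliminations, drugs or sedation, devices, and five yes/no mobility and cognitive items). Of these, 130 total 5 or less. Unstable gait is present in 17 + 8 + 3 = 28 of the 130, by ascending age band. A recent fall is present in exactly one: under 60, nothing else scored. These are counts of scoring patterns, not frequencies of patients.

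**Do the other criteria close the routes?** The disability exclusion in 4.5 does not reach a patient who walks unsteadily but unaided. The exclusion for an event moments before surgery would catch dizziness arising on the day, but not a known history or a past fall. ECOG 0–1 makes marked gait problems less likely, but it grades activity and asks about none of these conditions.

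**The case against.** The strongest reply is that the plan already layers its safeguards: ECOG 0–1, the two exclusions in 4.5, a stretcher bearer and a family member on the walk, and a scale in routine hospital use. Any additive scale lets a single item fall in its low band, and the documents give no evidence that these low-band patients fall more often. This limits the weight of the point. It does not remove it, because escorts support a patient on the way and do not select who walks.

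Several narrower objections stand:

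- The recent-fall route is nearly empty. Table 3 lists common drugs such as paracetamol and omeprazole, any one of which closes it.
- The practical effect of an item 8 Yes is unknown. A reader might infer that it counts for nothing at the bedside. The documents show only that no points or rule are printed; hospital routine may attach an effect.
- A reader might infer that the form already supplies everything needed for a tighter rule. It may not. Section 4.6 describes collecting the classification rather than item answers, item 8 is one answer for a whole list, and 4.2 calls the scale routine for patients over 60, so under-60s may not be scored routinely even though 4.4 requires a rating.
- Part of the urgency comes from the timing of consent, which is a separate matter. With consent before transport, this point would matter less.

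**Conclusion.** The point holds on the printed text. A total of 0 to 5 can clear for walking a patient with unaided unstable gait at any eligible age, or with known postural hypotension or dizziness. It can clear a patient with a recent fall in one narrow profile only. This rests on reading gear as gait, on the low-risk wording of 4.4, and on item 8 having no effect beyond what is printed. How many patients are affected cannot be derived from the documents.

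Three stronger readings are not supported. The scale does not admit a patient who has a recent fall, unstable gait and sensory impairment together; that total is at least 9. Section 5.1 does not claim that walking is free of risk, since it names a minimum risk of falls. And this is not a source of bias: both arms have the same eligibility rule, and alpha and power are untouched.

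It is a cheap participant-safety improvement for the sponsor to consider.

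**What to change.** Keep the 0–5 rule. Complete the scale for patients under 60 as well, as 4.4 already implies. Add one line to 4.5, applied before randomisation in both arms: exclude patients with unstable gait (item 6), with known postural hypotension or dizziness (checked in the chart, because item 8 is a single Yes or No), or with a fall in the last 6 months (item 2). Do not exclude visual or hearing impairment on its own; nothing in the documents argues for that on an escorted walk. Leave the other item 8 conditions as they are handled now.

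The cost is a short item-level chart check, some loss of candidates, and results that do not cover these patients. The loss is unknown. As an assumed range, take 2–10%. Section 7 shows five 4-month periods of data collection, or 20 months, so 176 patients need 176/20 = 8.8 a month. The candidates needed would rise to 8.8/0.98 = 9.0 up to 8.8/0.90 = 9.8 a month. At an unchanged rate, collection would instead last 20/0.98 = 20.4 up to 20/0.90 = 22.2 months.

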**4.3 Sample calculation**

Based on the results found by Kojima e*t al.* ([12](#_ENREF_12)) A sample size was calculated to compare proportions. Considering a α error of 0.05 and a power of 1 – β of 0.80, a sample size of 176 patients was reached, with 88 patients allocated to the stretcher group, and 88 patients allocated to the ambulation group.

